## 10. Risks to Subjects

|                                                                                                                                                                                                                                                                                                                                                                                                                                                                                                                                                                                                                                                                                                                                                                                                                 |                                         |
|-----------------------------------------------------------------------------------------------------------------------------------------------------------------------------------------------------------------------------------------------------------------------------------------------------------------------------------------------------------------------------------------------------------------------------------------------------------------------------------------------------------------------------------------------------------------------------------------------------------------------------------------------------------------------------------------------------------------------------------------------------------------------------------------------------------------|-----------------------------------------|
| 
a. List the reasonably foreseeable risks.
 
Potential risks. All participants will continue to receive their standard care from their medical providers. As described above, we will contact infants' primary care providers to notify them of the dyad's participation in the study. Our previous research found no increased risk of adverse events, or specifically failure to thrive, among those infants randomized to receive the multi-component prevention program. Given that the proposed study is focused on infant sleep and soothing, rather than focused on feeding, and is of significantly shorter duration than our previous multi-component trials, there is extremely minimal risk of insufficient weight gain and/or failure to thrive in the experimental group.
 |                                         |
| 
b. If applicable, describe any costs that subjects may be responsible for because of participation in the research.
                                                                                                                                                                                                                                                                                                                                                                                                                                                                                                                                                                                                                                                                               |  N/A |
| 
c. If applicable, describe risks to others who are not subjects.
                                                                                                                                                                                                                                                                                                                                                                                                                                                                                                                                                                                                                                                                                                                                  |  N/A |

## 11. Potential Benefits to Subjects

*Describe the potential benefits that individual subjects may experience from taking part in the research.*

Participants may experience improved health outcomes such as improved sleep and soothing, and healthier weight status during the first 16 weeks of life. All participants may benefit from sleep safety and those in the safety control arm may benefit from the home-based safety interventions. Childhood obesity may be prevented in some subjects in the study. There may also be positive effects for mothers' individual and relationship functioning.

## 12. Confidentiality

*Describe the procedures for maintenance of confidentiality.*

Subject confidentiality will be a priority for the research team, with prudent measures taken to ensure security of data and personal information. Upon enrollment, subjects will be assigned a study ID number which will serve as a code associated with all collected data. This code will be linked to the subject in only one document, the project directory, which will be password protected using an approved data management software system. Only pertinent study team members (PIs, coordinators) will have access to any and all data using a secure internet connection. Electronic and paper versions of de-identified data will be stored separately from any files that may contain subject names.

## 13. Consent Process

*If you are obtaining consent of subjects describe the consenting process.*

At the time of recruitment (AU newborn nursery), qualified mothers will be asked to read and sign a document indicating informed consent for herself and a separate parental permission document indicating consent for her infant to participate. The approved consent/permission documents will detail all study procedures and address incentives, risks, benefits, confidentiality and potential withdrawal. Mothers will have the opportunity to have any questions answered by the recruitment coordinator or PI prior to making the decision to enroll.

## 14. Compensation for Research-Related Injury

*This section is not required when research involves no more than Minimal Risk to subjects.* ☒ N/A

a. *Describe the available compensation in the event of research related injury.*

## 15. Resources Available

☐ N/A

a. *Describe the availability of medical or psychological resources that subjects might need as a result of an anticipated consequences of the human research.*

Although we do not anticipate any negative consequences of this research, all participants will receive a handout at the first visit with a list of community resources, including public health, mental health, food banks, shelters, division of labor, etc.

- b. Describe your process to ensure that all persons assisting with the research are adequately informed about the protocol, the research procedures, and their duties and functions.*

All study team members will be trained according to individual responsibilities with respect to the project and managed by the PIs and the Project Coordinator. Regular meetings of the core study team from each site (AU and UGA) will ensure efficient communication and management of personnel. All study team members will maintain appropriate training certifications.

Consistent with protocols used in the pilot trial and efficacious programs for rural African American families, the Community Research Associates (CRAs) who will serve as the Sleep-SAAF intervention home visit facilitators are African American community members from communities similar to the ones where the intervention will be implemented. However, CRAs will not reside in the same communities in which they are delivering the intervention. CRAs must have a minimum education level of high school graduation and are selected based on information from interviews and references that attests to their communication skills, engaging personalities, and ability to implement a structured program with fidelity. CRAs will receive 30 hours of training on the implementation of curriculum activities, guided practice in delivering and pacing curriculum segments, and facilitator self-care. They will work from a detailed manual that describes all facets of program delivery. Didactic material, role-playing exercises, and modeling will be used to teach the protocol for each session. Prior to implementation, CRAs must demonstrate mastery of the curriculum by passing a written test covering the session material. To ensure ongoing quality control and fidelity, CRAs will meet with the Project Coordinator and/or Intervention Coordinator weekly.

**Protocol Title:** Sleep-Safe: A Strong African American Families Study

**Principal Investigator:** [name]

## 1. Objectives

*Describe the purpose, specific aims, and hypothesis:*

Rapid weight gain in infancy is a risk factor for obesity and comorbidities later in the lifespan. This project is designed to test whether teaching mothers prompt, contingent, developmentally appropriate responsive parenting skills to soothe infants and promote adequate sleep can reduce rapid weight gain among African American infants living in the rural South. **Specific Aim 1: To assess the effects of responsive parenting, focused on infant sleep and soothing, on infant weight and reducing rapid weight gain from birth to 16 weeks among African American infants.** We hypothesize that infants in the sleep/soothe condition will have lower weight outcomes (i.e., BMI z scores, weight-for-length z scores, weight-for-age z scores) at age 16 weeks and gain weight more slowly compared to infants in a safety control condition. We consider whether weight-related factors (e.g., maternal pre-pregnancy BMI, gestational weight gain, intent to breast or formula feed, maternal smoking) moderate intervention effects. **Specific Aim 2: To assess effects of responsive parenting on parental and infant behaviors, and whether these mediate effects on infant growth.** We hypothesize that compared with control parents, parents in the sleep/soothe condition will show increases in responsive parenting, parenting self-efficacy, and the use of alternatives to feeding to soothe (white noise, pacifier, etc.), and decreases in feeding to soothe. Over time, infants in this condition will have longer sleep bouts and fewer feedings. These outcomes will be linked to healthier patterns of weight gain from birth to age 16 weeks, fully accounting for group differences. **Specific Aim 3: To examine moderation of intervention effects by individual and contextual factors.** We examine whether individual and contextual factors common among African American mothers moderate the effectiveness of the sleep/soothe intervention, informing development of future multi-component programs.

## 2. Background

*Describe the background and rationale for the study:*

This project is in response to the call for research to understand factors in infancy and early childhood that affect obesity development. Racial disparities in overweight among African American children compared to White children begin early in development and continue throughout the lifespan. During infancy, African American children have elevated rates of rapid weight gain and greater prevalence of high weight for length. Rapid weight gain is one of the most consistent risk factors associated with later overweight and obesity, showing associations with later overweight and obesity among toddlers, children, and young adults. Despite these well-established associations and the clear need for early intervention, there has been limited attention to developing interventions to prevent rapid weight gain among African American infants within underserved, low SES contexts. Accordingly, we propose to test whether teaching mothers prompt, contingent, developmentally appropriate responsive parenting skills to soothe infants and promote adequate sleep can reduce rapid weight gain among African American infants living in the rural South. Our examination of sleep and soothing evaluates a component of early obesity prevention programs that is promising, attractive to potential participants, and that may be particularly potent for African American infants in underserved, low SES contexts, making it the natural starting point for efforts to apply responsive parenting interventions in this high-risk context.

Findings from our two previous RCTs have provided evidence for efficacy of a multi- component responsive parenting (RP) program among middle income, predominantly White mother-infant dyads. Our team tested whether a multi-component RP program, delivered using home visits and including guidance on infant sleeping, soothing, active social play, and feeding, including the transition to table foods during the first year of life, could reduce rapid weight gain during infancy and overweight in early childhood. Relative to a home safety control, infants randomized to the RP program demonstrated significant differences in sleep behaviors at 8-, 16-, and 40-weeks, including longer nighttime sleep duration, had more consistent bedtime routines and earlier bedtimes, and were more likely to self-soothe to sleep without being fed. Relative to control, infants of parents receiving the RP program gained weight more slowly in the first months after birth, had lower weight-for-length percentiles at 1 year, and were less likely to be overweight at 1 year.

Shorter sleep duration is more prevalent among African Americans and is related to multiple adverse health outcomes including obesity. In infancy, sleep duration and feeding are tightly linked; sleep bouts tend to be interrupted by feeding; higher feeding frequency is associated with shorter sleep duration. The responsive parenting sleep/soothe intervention has the potential to alter parenting and infant behaviors (sleep, soothing, and feeding), directly affecting rapid weight gain and ultimately long-term weight outcomes, by promoting appropriate, prompt, and contingent soothing responses to infant crying. Focus groups with African American mothers suggest that the intervention will be well received, but the potential for moderation of effectiveness by individual (depressive symptoms) and contextual (poverty, relationship support) stressors common to African American mothers is currently unknown. Examining these factors as they relate to maternal response and rapid weight gain among infants will increase our understanding of how stress affects high-risk samples, potentially identifying additional intervention foci to be targeted in a subsequent multi- component program optimized for this high-risk population. Likewise, testing the mediational model that has guided this research to date and determining its applicability in this sociocultural context is an essential step in optimizing future interventions.

Our conceptual model is shown below. As shown in the Figure, we argue that a responsive parenting sleep/soothe intervention (Sleep SAAF) has the potential to alter parenting behaviors (responsive parenting, parenting self-efficacy, alternatives to feeding to soothe) and infant behaviors (sleep, soothing, and feeding). These in turn affect rapid weight gain and ultimately long-term weight outcomes. However, the effectiveness of this intervention may be affected by individual and contextual stressors common to African American mothers, including depressive symptoms, socioeconomic and race-based stressors, and a challenging interpersonal context.

**Figure 1. Conceptual Model: Early Factors Affecting Rapid Weight Gain among African American Infants**

[figure not shown]

### 3. Inclusion and Exclusion Criteria

*List the inclusion/exclusion criteria:*

A total of 375 African American mother-infant dyads will be recruited from AU's newborn nursery. Co-participation of the mother-infant dyad is a study requirement. Paternal involvement is voluntary, but not necessary. If fathers are interested in participating, they will sign separate consents.

#### **INCLUSION CRITERIA**

Eligible mother-infant dyads for this trial will meet the following criteria:

- 1) full-term infants ( $\geq 37$  0/7 weeks gestational age), apparently healthy and without significant morbidity
- 2) late pre-term infants (between 34 0/7 and 36 6/7 weeks gestational age), apparently healthy and without significant morbidity
- 3) singleton infant
- 4) nursery/NICU/maternity stay of 7 days or less
- 5) Mother at least 18 years of age
- 6) Mother self-identifies as African American
- 7) Mother is primiparous
- 8) Parental permission may be obtained from one parent to allow mothers who are 16 or 17 years of age to participate. Minor assent will also be obtained from 16 or 17 year old mothers at the time of enrollment. Mothers who are enrolled as minors but who become adult aged (18 years) while enrolled will be re-consented as adults before continuing in the study.

#### **C. EXCLUSION CRITERIA**

(not explicitly obvious from the inclusion criteria)

- 1) non-English speaking
- 2) infant birth weight <2500 grams (for full-term infants)
- 3) infant birth weight <2100 grams (for late pre-term infants)
- 4) presence of a congenital anomaly or neonatal physical or metabolic condition that significantly affects a newborn's feeding (e.g. cleft lip, cleft palate, metabolic disease)
- 5) any major maternal morbidities, pre-existing condition that would affect postpartum care or her ability to care for her newborn (e.g., narcotic drug use: heroin, cocaine, meth, pain pills, etc; on chemotherapy; uncontrolled MS; uncontrolled depression causing social service contact).
- 6) plan for newborn to be adopted
- 7) plan to move from area within four months of delivery
- 8) residence further than 75 miles from Augusta, GA
- 9) current or prior residence with another individual who participated or is currently participating in this study

#### 4. Number of Subjects/Records/Samples Collected

*Indicate the total number of subjects to be accrued/records reviewed/samples collected across all sites:*

Up to 375 mother-infant dyads and up to 375 fathers will participate in the study. All mothers will complete a series of questionnaires at enrollment and at 4 follow-up time points (study procedures described below). AU medical records will be used to gather selected demographic information on mothers (race, maternal age, gestational age, weight at delivery, address) and infants (date of birth, weight and length at delivery). Fathers will be invited to participate by the recruitment coordinator if they are present at the hospital, or by the study team if they are present at the first home visit (1 week postpartum). Fathers will sign separate consent form.

The study will be conducted over 4 years. The table below details the number of target participants per year:

| Year         | Mother-Infant Dyads | Fathers (Max #) | Research Interactions |
|--------------|---------------------|-----------------|-----------------------|
| Year 1       | 50                  | 50              | 200                   |
| Year 2       | 125                 | 125             | 500                   |
| Year 3       | 125                 | 125             | 500                   |
| Year 4       | 75                  | 75              | 300                   |
| Total | 375          | 375      | 1500           |

#### 5. Recruitment Methods

*Describe when, where, and how potential subjects will be recruited:*

Recruitment of 375 African American mothers and their infants will take place at Augusta University Medical Center in the Children's Hospital of Georgia's mother/baby nursery, when potential subjects are newly postpartum. A dedicated recruitment coordinator will be hired (AU staff) and trained to identify (via active medical chart data), screen, and enroll qualified subjects.

With approved Waivers of Consent and HIPAA Authorization, the recruitment coordinator will have access to electronic medical records systems and will complete the Sleep-Safe Screening and Eligibility Form Part 1 in order to pre-screen mothers and infants. The recruitment coordinator will approach those who match basic inclusion/exclusion criteria as detailed in Section 3 of this document. The recruitment coordinator will deliver an approved verbal script to pre-screened mothers to determine interest in participation. Interested mothers will respond to remaining screening questions (Screening and Eligibility Part 2) in order to confirm eligibility. Qualified and interested participants will then complete informed consent and move through the enrollment process with the recruitment coordinator.

## 6. Procedures Involved

- a. *Describe the procedures involved to include those procedures that are standard evaluation and/or care and those that are solely for research purposes:*

*All procedures are solely for research purposes. No contact and reduced contact interactions may be implemented in response to COVID-19. All interactions will include use of Personal Protective Equipment (PPE) and sanitization guidelines for both research associates and participants. A health screening will be administered prior to each visit and visits will be rescheduled if COVID-19 symptoms are endorsed.*

### Enrollment at AU Hospital Newborn Nursery (after delivery, Recruitment Coordinator):

1. Obtain maternal informed consent for mother-baby dyad
2. Obtain paternal informed consent for his own participation
3. Obtain selected demographic information (race, maternal age, gestational age, weight at delivery and (self-reported) pre-pregnancy weight) from the AU medical record system
4. Complete enrollment data collection forms
  - a. Chart abstraction form (coordinator completed)
  - b. Contact form
5. Measure weight (kg) and height (cm) of mothers and fathers (if father not present, will attempt to measure at subsequent visit)
6. Measure infant anthropometry: length (cm), weight (g), head circumference (cm), and mid-thigh circumference (cm).
7. Schedule the first research visit at the home for 1 week postpartum
8. Provide participants with overview of study safety guidelines

### Home Visit 1: (Home, 7-10 days postpartum, Community Research Associate (CRA))

1. Randomize and provide appropriate introductory materials (intervention or control) to mother-infant dyads
2. Complete questionnaire measures
3. Measure infant weight and length
4. Measure maternal weight
5. Measure paternal weight

### Home Visit 2: (Home, 3 weeks, CRA)

1. Deliver intervention or control group program
2. Complete questionnaire measures
3. Measure infant weight and length
4. Measure maternal weight
5. Measure paternal weight

### Home Visit 3: (Home, 8 weeks, CRA)

1. Deliver intervention or control group program
2. Provide mothers with activity monitors/diaries (to be picked up by study staff after 7 days' use)
3. Complete questionnaire measures
4. Measure infant weight and length
5. Measure maternal weight
6. Measure paternal weight

Telephone call: (12 weeks, CRA)

1. Scheduled phone call with mothers to check in and remind of 16 week assessment

Home Visit 4: (Home, 16 weeks, CRA)

1. Complete questionnaire measures
2. Measure infant weight, length, head circumference, and mid-thigh circumference
3. Measure maternal weight
4. Measure paternal weight
5. Complete questionnaire to determine interest in participation in one year follow-up visit and to update contact information

No-contact Home Visit 4: (Home, 16 weeks, CRA)

A no-contact visit will be offered to the 24 mother-infant dyads active in the study but unable to complete study procedures due to COVID-19 restrictions. After a precautionary health screening and providing instructions to participant, a research associate will place sanitized materials (iPad, infant scale, adult scale) outside the door to the home. The participant will then retrieve these materials and complete study procedures inside the home. The research associate will be available by phone to assist if needed, and will retrieve materials once replaced outside by participant. There will be no face-to-face contact between the research associate and the participant.

1. Complete questionnaire measures
2. Measure infant weight
3. Measure maternal weight
4. Complete questionnaire to determine interest in participation in one year follow-up visit and to update contact information

Researcher will request permission at the time of consent to photograph mother and/or infant during a research visit. These photos would be used in conjunction with presentations or publications related to this study.

\*\*\* Table 1 provides additional details on scheduled assessments at each time point. We provide additional information on the intervention and control group materials in the following section on study design. Participating fathers will also complete measures listed in parent outcomes, stress-support moderators, and demographics. Refer to Appendix 4 – Measures\*\*\*

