For any individual child that meets initial screening criteria for growth concerns, numerous factors will be considered in determining whether the child's growth is problematic and/or related to study interventions. Examples of such factors include genetic potential based upon parental size, the participant's linear growth, feeding mode (breast milk vs. formula), and interval illnesses. If either the primary care provider or the study investigators believe that it is possible that these growth patterns are a negative result from study participation, the child will be withdrawn from the study.

Additional details regarding growth monitoring are included in Section 8 (Provisions to Monitor the Data to Ensure the Safety of Subjects) below.

*d. Describe the duration of an individual subject's participation in the study and the time involved:*

Mother-infant dyads are enrolled for a period of 16 weeks. Interactions include initial enrollment and 4 subsequent research and/or intervention visits to the family's home. Enrollment will take place within 24-72 hours of delivery (while the mother is admitted to the newborn nursery) and participation will continue until the infant is 16 weeks (not more than 30 weeks) of age. Initial enrollment procedures will take 60-90 minutes; each following study visit will take 90-120 minutes.

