First, we will examine differences in BMI and other weight outcomes at 16 weeks between the Sleep SAAF group and the control group using a linear mixed-effects model. The linear mixed-effects model will include intervention group and infant weight at age 1 week adjusted for gestational age. These analyses will test whether the Sleep SAAF group and the control group differ in their weight outcomes at age 16 weeks, which has previously been linked to child obesity risk at age 2 years.

Next, we will consider growth models that examine rate of change in weight from birth to 16 weeks. We will conduct growth curve analyses using hierarchical linear modeling to test whether the Sleep SAAF and control groups differ in their rate of change in weight over time. The model will include intervention group, time of growth measure, and infant weight adjusted for gestational age. These analyses will evaluate whether the Sleep SAAF group shows less of an increase in weight over time compared to the safety control group.

As an additional test of rapid weight gain, weight gain z-scores will be calculated for each measurement subsequent to the first intervention session at age 3 weeks (8 weeks and 16 weeks). Rapid weight gain scores will be calculated as an increase in weight-for-

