
|                                                                                                                                                                                                                                                                                                                                                                                                                                                                                                                                                                                                                                                                                                                                                       |                                 |
|-------------------------------------------------------------------------------------------------------------------------------------------------------------------------------------------------------------------------------------------------------------------------------------------------------------------------------------------------------------------------------------------------------------------------------------------------------------------------------------------------------------------------------------------------------------------------------------------------------------------------------------------------------------------------------------------------------------------------------------------------------|---------------------------------|
| 
The primary outcomes for this study will be BMI z scores at 16 weeks (Specific Aim 1) and parent and infant behaviors at 8 weeks and 16 weeks (Specific Aim 2). We used G Power 3.1.9.2 to estimate the smallest intervention effect size we can detect with 80% power, a 5% two-tailed Type 1 error rate, and two groups of 175 each (conservatively assuming 10% attrition over the course of the study). We can achieve 80% power with an effect size <math>d</math> of 0.34. Our recent research showed an effect size of approximately 0.4 for infant nighttime sleep duration at 8 weeks and for infant conditional weight gain at 6 months, suggesting that we will have sufficient power in our sample to detect intervention effects.
 |                                 |

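### Weight-only no-contact visits give no 16-week BMI z, late visits have no analysis window, and the stated primary model does not name the BMI z values from 1, 3 and 8 weeks

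*Supplement*

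**What the plan says.** All references are to the latest protocol version in the Supplement.

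- **Outcome.** Section 7.b: "The primary outcomes for this study will be BMI z scores at 16 weeks" (Specific Aim 1). Section 6.a, Infant Growth, derives BMI z from weight and recumbent length, standardised for age and sex.
- **No-contact visit.** Section 6.a, No-contact Home Visit 4: "A no-contact visit will be offered to the 24 mother-infant dyads active in the study" who could not complete procedures because of COVID-19 restrictions. Staff "place sanitized materials (iPad, infant scale, adult scale) outside the door to the home", and the mother does the measuring. Infant weight is listed; length is not. The standard 16-week visit lists both.
- **Timing.** Section 6.d: "participation will continue until the infant is 16 weeks (not more than 30 weeks) of age". No narrower window for the 16-week measurement appears. Section 6.b places the last session at 8 weeks.
- **Model.** Section 7.a, Specific Aim 1: "The linear mixed-effects model will include intervention group and infant weight at age 1 week adjusted for gestational age". Missing data are to be handled by full-information maximum likelihood. Earlier BMI z is not named in this model or among the further covariates to be considered.
- **Earlier data.** Table 1 schedules infant anthropometry at 1, 3, 8 and 16 weeks.

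**The concern.** The plan relies on a likelihood method to make full use of partial data, but the model it writes down gives that method little to work with. Suppose each infant has one outcome, BMI z at 16 weeks, and the only predictors are arm and 1-week weight. An infant without that outcome then contributes essentially nothing to the treatment contrast, even if BMI z was measured three times before. The baseline value of the outcome is not used either; 1-week weight stands in for it.

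The time point is also loose. A value counted as 16-week could come 8 weeks (16 − 8) or as much as 22 weeks (30 − 8) after the last session. No rule says which late values count, or how weight-only visits and mother-measured weights are handled. Left open, these choices could be made after results are seen.

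**Working it through.** **1. The plan's own figure.** Section 7.b assumes "80% power, a 5% two-tailed Type 1 error rate, and two groups of 175 each", "conservatively assuming 10% attrition over the course of the study", and states a detectable d of 0.34. For a two-sample comparison, approximately,

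d = (z₀.₉₇₅ + z₀.₈₀) × √(2/n per arm).

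The figures in steps 1 and 3 use the exact noncentral t version.

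- 175 per arm: d = 0.300.
- 175 × 0.9 = 157.5 per arm: d = 0.317.
- 150 × 0.9 = 135 per arm: d = 0.342.

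So 0.34 does not follow from 175 per arm. It fits 150 per arm less 10%. The discrepancy is conservative and is a separate matter. Because Section 4 plans up to 375 dyads and the power section uses 350, both bases are shown.

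**2. Share without the primary outcome.**

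- 24/375 = 6.4%; 24/350 = 6.9%.
- If none of the 24 overlaps the 10% attrition: (37.5 + 24)/375 = 16.4%; (35 + 24)/350 = 16.9%. These are upper bounds.

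**3. Effect on detectable d and on power at d = 0.34.**

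| Basis | n per arm after 10% attrition | d | Power | n per arm after also losing 24 | d | Power |
|---|---|---|---|---|---|---|
| 375 | 168.75 | 0.306 | 0.876 | 156.75 | 0.317 | 0.851 |
| 350 | 157.5 | 0.317 | 0.853 | 145.5 | 0.330 | 0.824 |

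If all 24 fell in one arm on the 350 basis (157.5 against 133.5), d = 0.331 and power = 0.821.

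**4. What earlier values could recover.** The documents give no correlation r between visits, so r is assumed. Take the 350 basis and suppose all 24 have an 8-week BMI z. With the earlier value observed in 157.5 per arm and the 16-week value in 145.5,

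variance per arm ∝ (1 − r²)/145.5 + r²/157.5.

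| r | Effective n per arm | d (normal approximation) |
|---|---|---|
| no recovery | 145.5 | 0.329 |
| 0.3 | 146.5 | 0.327 |
| 0.5 | 148.3 | 0.325 |
| 0.7 | 151.1 | 0.322 |

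The variance saving runs from 1 − 145.5/146.5 = 0.7% to 1 − 145.5/151.1 = 3.7%.

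**5. What a baseline BMI z could add.** Adjusting for a baseline value with correlation r multiplies d by √(1 − r²). At 145.5 per arm, 0.330 becomes 0.314, 0.285 or 0.235 for r = 0.3, 0.5 or 0.7. Here r is the correlation between 1-week and 16-week BMI z. The comparison is with no adjustment, so 1-week weight, already in the model, may deliver part of this gain. The 3- and 8-week values follow randomisation and belong in the model as outcomes, not covariates.

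**The case against.** **The model may already be longitudinal.** The text calls it a mixed-effects model, and Specific Aim 2 applies the same model to 8 and 16 weeks. Repeated BMI z may have been intended. This stands as an ambiguity. But the Aim 1 description lists no time term, whereas the growth model next to it does, and it names no earlier BMI z. One cannot say that the plan certainly reduces to complete cases, only that it does so in effect as written.

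**Age at measurement.** A reader might infer that the primary analysis ignores age. It does not: BMI z is standardised for age and sex, and the separate growth model includes time of measurement. What remains is that late values differ in time since the last session. The 30-week figure is a cap on participation, and the number of late visits is unknown.

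**The 24 is a ceiling.** The visit is offered, not assured, and some of these dyads may fall within the planned attrition. Section 6.a, under the COVID-19 Impact Survey, says only that they were active during the hold. It does not show that each had completed an 8-week visit, so recovery for this group is not assured.

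**Power and bias.** A reader might infer an underpowered trial or a biased comparison. The documents support neither. Power at the stated d stays above 80%, and the loss comes from a general hold on face-to-face research, with nothing to show that it differed by arm.

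**Existing safeguards.** Weight-for-age z at 16 weeks is already a named outcome, and using 1-week weight as covariate costs precision, not validity. Both points stand.

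**Conclusion.** The point holds as a matter of precision and definition. Up to 24 dyads can finish with a visit that gives no BMI z, the 16-week time point has no analysis window, and the stated primary model leaves out BMI z values that the schedule already collects. The cost is a rise in detectable d of about 0.011 (0.306 to 0.317) on 375 dyads or 0.013 (0.317 to 0.330) on 350.

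These figures assume that all 24 are lost in addition to 10% attrition. The gain from earlier values rests on assumed correlations: small if only the 24 are recovered, and possibly larger from a baseline BMI z. The change is worth making because it needs no new data, and because the handling of late and weight-only visits should be fixed before the results are known.

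**What to change.** In Section 7.a, Specific Aim 1:

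1. Make the primary analysis a repeated-measures model of BMI z at 1, 3, 8 and 16 weeks with unstructured covariance. Treat 1 week as a common baseline or as a covariate, keep the adjustment for gestational age, and take the treatment contrast at 16 weeks.
2. State an analysis window for the 16-week visit. Put values outside it in a sensitivity analysis or in the existing growth model, which includes time of measurement. Do not place them in the 16-week cell: an unstructured visit covariance has no slot for a value at another age.
3. State that a weight-only visit leaves 16-week BMI z missing, and report the already planned 16-week weight-for-age z with and without mother-measured weights.

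The cost is analysis wording and a little more code, with no extra visits or measurements. The downside is that a few late values leave the primary 16-week cell.
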